#### Exclusion criteria

SLED initiated for non-AKI-related indication (such as concurrent intoxication; treatment of hypothermia)Receiving chronic dialysis treatmentsHistory of allergic reaction to albuminPregnancyPatients with contraindications or known objections to blood transfusions

### Intervention

Participants will be randomized to receive either albumin (25%) boluses or normal saline placebo boluses during their SLED treatments in ICU (i.e., once randomized, the same fluid will be given during all subsequent SLED treatments for that patient). Since both interventions (albumin (25%) boluses and normal saline placebo boluses) will be administered by ICU nurses, we do not expect adherence to be a major issue. Nonetheless, we will monitor adherence on an ongoing basis as it is possible that the mid-treatment boluses are more likely to be missed if there is no hemodynamic instability observed during treatment. This pilot trial has no prohibitions in usual care, including physician-prescribed albumin or other fluids.

### Outcome measures

#### Feasibility

Recruitment rate, adherence to intervention, and completeness of follow-up are the principal outcome measures. This study aims to establish that (a) the team can randomize 30 patients into this trial over the study period and (b) trial participants have > 90% adherence to receiving albumin (25%) or normal saline placebo boluses during SLED treatments, as assigned through randomization. For this outcome, each SLED treatment (rather than patient) will be the unit of analysis.

### Efficacy

Efficacy measures are to be assessed in an exploratory manner only. Efficacy outcomes will not be used to determine whether a subsequent, larger trial to assess efficacy outcomes is warranted. They will primarily be collected in order to identify any challenges with respect to data collection itself. Efficacy outcomes to be assessed by this pilot trial include (a) the “overall fluid removal” (i.e., percentage of target ultrafiltration achieved, calculated as the actual ultrafiltration volume divided by the target (ordered) ultrafiltration volume), (b) hemodynamic stability (i.e., initiation or increase in vasopressor dose(s) at the end of treatment, onset of MAP < 55 mmHg during treatment, absolute drop in MAP of ≥ 20 mmHg), (c) hospital length of stay, (d) ICU length of stay, (e) death at 1 year, and (f) dialysis dependence at 1 year. Efficacy measures (a) and (b) will be assessed at the level of SLED treatments while (c), (d), (e), and (f) will be analyzed at the patient level.

### Measurement

#### Albumin (25%) boluses

Participants randomized to this arm will receive 100 mL of intravenous albumin (25%) at the initiation of SLED and another 100 mL after 4 h of treatment (the half-way point of standard 8 h treatment). Both albumin and saline infusions will be administered over 15 min. The albumin boluses will be supplied through Canadian Blood Services.

#### Normal saline placebo boluses

Participants randomized to this arm of the trial will receive 100 mL of normal saline placebo at the initiation of SLED and another 100 mL after 4 h of treatment. The research pharmacy at The Ottawa Hospital will prepare the placebo saline boluses.

#### Co-interventions

As the development of severe or prolonged hypotension during treatment (for reasons related or unrelated to SLED) may necessitate urgent treatment, co-interventions will be permitted and tracked during the trial. This includes starting or increasing vasopressors and the administration of extra albumin (or other IV fluid) boluses during SLED, at the discretion of the treating physician.

### Ethical issues and trial registration

The pilot trial will be conducted in accordance with Health Canada’s Good Clinical Practice guidelines, the current Declaration of Helsinki, and the Tri-Council Policy State: Ethical Conduct for Research Involving Humans. The patients in this study are often not competent enough to consent to research due to their illness; many are intubated or are on respirator. Given this, we will have to seek consent for their participation from their designated substitute decision maker. Patients’ family who agree to participate in this study will provide a written informed consent by the research coordinator, included as Additional file 1. If during anytime of the study the patient regains competency, they will be provided with information, as is presented in the pamphlet included as Additional file 2, but will not be required to formally consent unless the intervention is ongoing (i.e., they are still receiving SLED). In most cases, patients are very unlikely to regain competency while still receiving SLED as it is only used as RRT when there is hemodynamic instability and patients tend to be severely ill and intubated. Patients can withdraw from the study at any time. Any data that were collected will then be discarded, destroyed, and not used in the study. All patients will be informed that they can withdraw from the study at any time. The study protocol, informed consent forms, and information pamphlet have been approved by the Ottawa Health Science Network Research Ethics Board. The trial is registered at the US National Institutes of Health (ClinicalTrials.gov) # NCT03665311.

Access to medical records and study data will be limited to authorized personnel listed on the study delegation log or permitted by the study agreement. Access to electronic data will be password protected and auditable, electronic data will be stored on a hospital network with firewall and security back-up measure in place, and paper copies of the study data will be stored securely in locked cabinets and in locked offices.

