### Sample size and analytic plan

A total of 30 patients with AKI requiring treatment with SLED (by definition, Kidney Disease Improving Global Outcomes (KDIGO) stage 3 AKI) will be recruited and followed up for this study over the period of 7–14 months at the Ottawa Hospital’s intensive care unit. As this is a pilot study, we do not include a formal sample size calculation. We felt that including 15 patients in each group would inform us about the practical aspects of conducting a larger RCT with respect to study procedures, recruitment, and data collection. Of particular note, this includes determining the average number of SLED sessions received per patient (which will inform the analysis plan for efficacy outcomes for a larger study).

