### Progression criteria

We will apply the following criteria to make the decision that a definitive trial is worth pursuing, depending on funding and if we can successfully recruit more than 25 patients and enroll 15% of all eligible patients, of whom less than 10% have complications related to the intervention. This pilot trial is to test the study plan and find out whether enough participants will join a larger study and accept the study procedures. The results will be used as a guide for larger studies, and we plan to report our study findings in open-access peer-reviewed journals.

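### Destroying all data from patients who withdraw conflicts with the protocol's own follow-up, adherence and safety measures, and a single deletion could turn a failed complication criterion into a pass

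*Protocol article*

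**What the plan says.** The section Ethical issues and trial registration of the protocol article states: "Patients can withdraw from the study at any time". The next sentence fixes what happens to the record: "Any data that were collected will then be discarded, destroyed, and not used in the study". The rule covers everything collected, with no carve-out for adverse events, session adherence or follow-up status. No other section supplies one.

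Three other places depend on the data that this rule removes:

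- Outcome measures, Feasibility: "Recruitment rate, adherence to intervention, and completeness of follow-up are the principal outcome measures". The same section sets an adherence aim above 90%, with the SLED treatment as the unit.
- Progression criteria: a definitive trial is worth pursuing, subject to funding, if the team can "successfully recruit more than 25 patients and enroll 15% of all eligible patients, of whom less than 10% have complications related to the intervention".
- Study measurement and patient safety: adverse events are to be monitored and tracked for the whole trial.

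The planned size is 30, 15 per group, and the article says: "As this is a pilot study, we do not include a formal sample size calculation".

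**The concern.** Withdrawal can come after randomisation and after boluses have been given, and with outcomes at 1 year it can come long after treatment has ended. Deleting such a patient removes evidence that the pilot was set up to collect. A withdrawal is itself a form of incomplete follow-up and bears directly on whether participants accept the procedures, yet the rule erases it. A patient who has a related complication and then withdraws leaves both the numerator and the denominator of the complication proportion.

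With only 30 patients and a threshold of 10%, that proportion is decided by one or two people. A safety criterion in a go/no-go decision could therefore be met because of the deletion rule alone. A later analysis plan cannot repair this, since destroyed data cannot be analysed.

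**Working it through.** **Inputs from the protocol article.** Planned total 30, 15 per group (Sample size and analytic plan). Complications must be below 10% of those enrolled, and recruitment above 25 (Progression criteria). Adherence aim above 90% per SLED treatment (Feasibility). Withdrawal rate and complication rate: not given.

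**The plan's own figure.** 15 × 2 = 30, which reproduces the stated size. There is no power calculation to reproduce.

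**Complication criterion.** With c complications among 30 patients, the proportion is c/30. The criterion needs c/30 < 0.10, so c = 2 passes (2/30 = 6.7%) and c = 3 fails (3/30 = 10.0%). If w of the c patients withdraw and are deleted, the reported proportion is (c − w)/(30 − w):

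| Complications c | All data kept | Deleted w | After deletion |
|---|---|---|---|
| 3 | 3/30 = 10.0%, fails | 1 | 2/29 = 6.9%, passes |
| 4 | 4/30 = 13.3%, fails | 2 | 2/28 = 7.1%, passes |
| 5 | 5/30 = 16.7%, fails | 3 | 2/27 = 7.4%, passes |

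The opposite flip is much harder. Starting from 2/30, deleting patients without complications reaches 10% only at 2/20, that is, after 10 withdrawals.

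**Follow-up.** If 4 of 30 withdraw and the other 26 complete, follow-up is 26/30 = 87%. After deletion it is 26/26 = 100%.

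**Adherence.** Assume equal numbers of sessions, s, per patient and 27s of 30s sessions adherent. That is exactly 90%, which misses the aim of more than 90%. Deleting one patient who missed every session gives 27s/29s = 93.1%, which meets it.

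**How much the complication criterion could shift.** This needs assumed rates. Let each of 30 patients have a related complication with probability p. Those with a complication withdraw with probability q and the others with probability r. Summing the binomial probabilities over all outcomes in which the reported proportion is below 10% gives the chance of passing:

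| True rate p | All data kept | q = r = 10% | q = 30%, r = 5% | q = 50%, r = 5% |
|---|---|---|---|---|
| 10% | 41.1% | 48.5% | 64.9% | 81.2% |
| 15% | 15.1% | 21.0% | 37.7% | 60.6% |
| 20% | 4.4% | 7.4% | 18.9% | 41.0% |

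The shift is modest if withdrawal is unrelated to complications and large if it is linked to them. The protocol gives no basis for choosing a column.

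**The case against.** The strongest case on the other side is about reach.

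- **Recruitment.** A reader might infer that deletion also lowers the recruitment count, for example that 27 randomised less 2 withdrawn leaves 25 and fails the requirement of more than 25. The text does not support this. The count is defined by recruiting, enrolling and randomising, all of which precede withdrawal. The web-based randomisation system and the pharmacist's allocation record exist apart from the outcome data, and nothing says they are erased. This objection stands.
- **Progression.** Follow-up and adherence do not appear in Progression criteria, and follow-up has no stated threshold. The 87% against 100% example distorts a principal outcome but flips no decision. This also stands.
- **Who withdraws.** A reader might infer that the rule removes precisely the patients with complications. No section links the two. The ethics section expects few patients to recover decision-making capacity during SLED, and the only adherence risk named under Intervention is a missed mid-treatment bolus. Withdrawal through a substitute decision maker remains possible.
- **Arm comparison.** Efficacy is exploratory and plays no part in the progression decision, and the clinical team is blinded. Bias between arms is a minor point here.
- **Safety reporting.** The commitments to Good Clinical Practice and to adverse event tracking mean that one cannot say events will disappear. What can be said is that those commitments and the destruction rule are not reconciled.
- **Consent.** The rule is a commitment that the ethics board approved, and the consent form is not shown. That limits how the rule may be changed. It does not make the rule compatible with the outcomes.

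**Conclusion.** The point holds in a limited form. As written, the destruction rule conflicts with adherence and completeness of follow-up as principal outcomes, with adverse event tracking throughout the trial, and with the complication criterion for progression. For that criterion, one deletion is enough at 30 patients: 10.0% becomes 6.9%. This assumes that the rule is applied literally and that the withdrawn patient had a related complication.

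The documents show that a flip is possible, not that it is likely, because they give neither a withdrawal rate nor a complication rate. Follow-up and adherence can be made to look better than they were, but neither decides progression. The recruitment count need not change. The matter deserves correction before recruitment opens because the loss is irreversible.

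**What to change.** Amend the protocol and the consent wording as follows:

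1. Withdrawal ends study participation and new data collection. Data collected up to that date, including adverse events and session adherence, are retained and analysed as far as consent and the ethics board allow.
2. Every randomised patient stays in the randomised count.
3. Withdrawals are reported by arm, with timing and, where given, reason, as a feasibility outcome.
4. Where a patient or substitute decision maker explicitly asks for removal, the individual data are deleted and only a de-identified count by arm is kept. The complication criterion is then reported under best and worst cases for the deleted patients. For example, with 2 complications among 29 retained and 1 deleted, the range is 2/30 = 6.7% to 3/30 = 10.0%, and the report would show that the decision depends on the missing patient.

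The cost is an ethics amendment, since the current wording is already approved. Deletion also becomes something that must be requested rather than the default. The right to withdraw is unchanged.

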### Sample size and analytic plan

A total of 30 patients with AKI requiring treatment with SLED (by definition, Kidney Disease Improving Global Outcomes (KDIGO) stage 3 AKI) will be recruited and followed up for this study over the period of 7–14 months at the Ottawa Hospital’s intensive care unit. As this is a pilot study, we do not include a formal sample size calculation. We felt that including 15 patients in each group would inform us about the practical aspects of conducting a larger RCT with respect to study procedures, recruitment, and data collection. Of particular note, this includes determining the average number of SLED sessions received per patient (which will inform the analysis plan for efficacy outcomes for a larger study).

#### Baseline analyses

Baseline characteristics of patients in the two treatment arms will be assessed using frequency distributions and univariate descriptive statistics including measures of central tendency and dispersion.

#### Feasibility

For the feasibility outcome of recruitment, we will calculate the proportion (and 95% confidence interval) of all eligible SLED patients who are randomized into the trial. In addition, we will calculate the proportion of SLED patients that are eligible but declined to consent, eligible but not approached, and not eligible.

#### Efficacy

Efficacy outcomes in the pilot trial will be described using proportions for dichotomous variables. Continuous variables will be described using medians and interquartile ranges (IQRs). According to an assessment of the distribution of the efficacy outcomes data collected, appropriate statistical tests will be conducted to compare all efficacy outcomes between groups (with 95% confidence intervals). As mentioned, these outcomes will be underpowered for a meaningful comparison and are being conducted to help us design a multi-center pilot trial.

All analyses will be conducted using SAS® software Version 9.3 (Cary, NC, USA).

### Assignment of interventions and data management

The randomization process will consist of a computer-generated random listing of the treatment allocations. This random listing will be generated for four consecutive patients at a time, separately, at each of the two medical-surgical ICUs at The Ottawa Hospital (i.e., random assignment of individual patients to either treatment allocation *within* each block of four). This randomization will be accessed by the research pharmacist after a patient is enrolled as well as the assignment of intervention. After screening the patient for eligibility and obtaining informed consent, the study coordinator will provide the subject’s unique identification as well as a confirmation of consent and eligibility. The randomization and data management will be overseen by the Data Management Services (DMS) of the Methods Centre for the Clinical Epidemiology Unit of the Ottawa Hospital Research Institute. The DMS is responsible for designing, coding, implementing, and maintaining a secure web-based randomization system for the randomized controlled trial.

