### Study population and timeline

The research coordinators will screen daily for patients that are in ICU to determine whether or not a patient is eligible for this pilot trial. This screening includes review of patient charts and discussion with nurses and physicians from the Circle of Care. The ICU is a closed unit in the sense that it is the same team recruiting for all studies in the unit. This pilot trial will require 24 months to complete. The participant recruitment and follow-up will take place during month 7 to 21 included as Table 1.

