### Blinding

Only the research pharmacist responsible for preparing the albumin and placebo will access the computerized random allocation assignment. They will be the only member of the research team to record the allocation.

Blinding of the intervention is difficult since albumin (25%) must be stored in glass containers and is yellow in color while normal saline comes in infusion bags and is transparent. For this pilot trial, the blinding involves administering the placebo (normal saline) in similar glass bottles to those used for the albumin. Both the albumin fluid and placebo will be prepared in advance of administration by the research pharmacist, covered with opaque bags, and primed into opaque intravenous tubing. Furthermore, all members of the clinical and research team will be blinded except the research pharmacist.

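### A fixed, published block of four within each ICU would let about three in ten assignments be deduced if the bedside blind failed completely, and fewer if it leaked only in part

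*Protocol article*

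**What the plan says.** The section on assignment of interventions and data management describes the list: "This random listing will be generated for four consecutive patients at a time, separately, at each of the two medical-surgical ICUs". It goes on to explain this as "random assignment of individual patients to either treatment allocation" within each block of four. No second block size and no random variation of size is mentioned, and the size is printed in the article.

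The article does not write out a 2:2 split. The sample size section implies it: "A total of 30 patients with AKI requiring treatment with SLED" are planned, and "We felt that including 15 patients in each group would inform us about the practical aspects of conducting a larger RCT".

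The Blinding section states the difficulty openly: "Blinding of the intervention is difficult since albumin (25%) must be stored in glass containers and is yellow in color", whereas saline is transparent. It then gives countermeasures. Saline goes into similar glass bottles. Both fluids are prepared in advance by the research pharmacist, "covered with opaque bags, and primed into opaque intravenous tubing". Only that pharmacist sees the allocation, and all other clinical and research staff are to be blinded. The assignment section adds that the list is consulted only after a patient has been enrolled.

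On recruitment, the section on study population and timeline says that coordinators screen daily, partly by talking with the treating nurses and physicians, and that "it is the same team recruiting for all studies in the unit".

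**The concern.** Restricting the list to the pharmacist, and opening it only after enrolment, stops anyone from reading the next assignment. It does not stop anyone from inferring it from earlier patients. With a known block of four, that inference is blocked only by the bedside blind, the one safeguard the article describes as hard to achieve. Chances to notice recur, because each patient is due two boluses per session and keeps the same fluid in all later sessions. What bedside staff notice could reach the recruiters, who speak with them when screening.

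Two things are at stake. First, a recruiter who knows or suspects the next arm can decide whom to approach. That could alter the make-up of the arms and the share of eligible patients enrolled, which is a progression criterion. Second, recognising one patient gives information about others in the same block, so a local failure of the blind spreads. Recruitment and blinding are both named in the pilot's primary aim, and the scheme tested here may carry over to the larger trial.

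**Working it through.** The article gives no figure for predictability, so there is nothing of its own to reproduce.

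**Inputs from the article:** block size 4, fixed; a separate list in each of two ICUs; 30 patients, 15 per group.

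**Assumptions:** each block is split 2:2; the observer knows where each block starts; 15 patients per ICU (other splits below); each earlier patient in a block is recognised independently with probability *q*.

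**Step 1: full recognition (*q* = 1), one complete block.** There are six equally likely orders: AASS, ASAS, ASSA, SAAS, SASA, SSAA (A albumin, S saline). The third assignment is forced only when the first two match, in 2 of 6 orders. The fourth is always forced. The best guess is the arm with more places left.

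| Position in block | Probability of being certain | Probability that the best guess is right |
|---|---|---|
| 1 | 0 | 1/2 |
| 2 | 0 | 2/3 |
| 3 | 1/3 | 1/3 × 1 + 2/3 × 1/2 = 2/3 |
| 4 | 1 | 1 |
| Mean | (4/3)/4 = 33.3% | (17/6)/4 = 70.8% |

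**Step 2: 30 patients, 15 per ICU.** Each ICU completes three blocks and enters three patients into a fourth.

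- Certain: 3 × 4/3 + 1/3 = 4.33 per ICU, so 8.67 of 30 = 28.9%.
- Best guess right: 3 × 17/6 + (1/2 + 2/3 + 2/3) = 10.33 per ICU, so 20.67 of 30 = 68.9%.
- Over all splits of 30 patients between the ICUs, the certain count lies between 8.67 and 9.33 (28.9% to 31.1%).

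**Step 3: partial recognition.** An assignment is certain only if both earlier patients of the exhausted arm were recognised, which has probability *q*². The share in complete blocks is therefore *q*²/3, and the count with 15 per ICU is 8.67 × *q*².

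| *q* | Certain, complete blocks | Expected certain of 30 (15 per ICU) |
|---|---|---|
| 1 | 33.3% | 8.7 |
| 0.75 | 18.8% | 4.9 |
| 0.5 | 8.3% | 2.2 |
| 0.25 | 2.1% | 0.5 |

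**Step 4: randomly varying blocks.** This was simulated with 15 per ICU, full recognition, and an observer who knows that the possible sizes are four and six but not their order. Certain assignments fall to about 6% (about 1.8 of 30). The best guess is right about 68% of the time, against about 69% with fixed blocks of four.

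**The case against.** The strongest reply is that every route to harm needs the blind to fail first. The word difficult in the Blinding section describes the untreated products and introduces the countermeasures; nothing in the article says that the blind is expected to fail. The ICU nurses give the fluid and the coordinators recruit, so knowledge would have to be gained at the bedside, passed on, and tracked within a block. With 15 patients per ICU over months 7 to 21 (15 months if both ends count), each ICU enrols about one a month and a block spans about four months, though the 7–14 months in the sample size section would shorten this. Efficacy is exploratory and does not decide whether a larger trial follows. The progression criteria are pooled across arms, and patients who were eligible but not approached will be counted.

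Most of this stands, and it limits the size of the point. It does not remove it: a concealment scheme should still work when masking leaks, and the approach decision feeds the enrolled proportion.

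Two stronger readings do not hold. A reader might infer that staff who see through the fluid would know upcoming assignments with certainty. Step 1 shows otherwise: the first two patients of a block are never certain, and even under full recognition about 71% of assignments (15 per ICU) remain uncertain. A reader might also blame the block size for changes in open-label albumin or vasopressors, which the Co-interventions section leaves "at the discretion of the treating physician". Such changes follow mainly from unmasking the patient being treated and could occur under any scheme; the block size adds only inference about others in the block.

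**Conclusion.** The point holds as a conditional weakness. The fixed, disclosed block makes concealment depend on the bedside blind. The worst case with 15 patients per ICU is about 29% of assignments deducible, 8 to 9 of 30. If each earlier patient is recognised half the time, the expected number is about 2 of 30. The true recognition probability is unknown and the article gives no basis for choosing one, so the range should be reported rather than its upper end. The figures also rest on the implied 2:2 split and on an observer who knows where blocks begin. The consequence is modest in a 30-patient pilot with exploratory efficacy, but it touches recruitment and blinding, which the pilot sets out to test, and the remedy is cheap.

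**What to change.** Generate the list within each ICU in permuted blocks of randomly varying size, for example four and six. Withhold the sizes and their order from recruiting and clinical staff, and from public documents, until enrolment ends. Size four is already in print, but the gain does not depend on hiding it: the 6% figure assumes that the possible sizes are known and only their order is not.

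The benefit is mainly fewer certain assignments; the best-guess rate hardly moves, so the masking measures remain essential.

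The cost is a setting in the web-based randomisation system that the article describes, and the article says that recruitment is still to begin. The statistical cost is slightly looser balance. With 15 per ICU, fixed blocks of four leave each ICU at 2:1 in its last, incomplete block, so the arms end at 15:15 or 16:14. With sizes four and six, an ICU can end three patients into a block of six at 3:0, so the extreme is 18:12, two more patients in the larger arm. In a simulation of 40,000 trials, a split wider than 16:14 occurred in about 2%.
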